**Fig. 3 Fig3:**
[figure not shown]
CONSORT diagram

After the 3-month follow-up, qualitative interviews will be conducted with intervention facilitators, outcome assessors, trial participants and family members to gain knowledge on implementation processes. The interviewers will be unmasked and will not be involved in outcome assessments.

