**Fig. 2 Fig2:**
[figure not shown]
SPIRIT figure outlining the schedule of enrolment, intervention, and assessments

Beyond the primary and secondary outcomes, sociodemographic data will also be collected at baseline, and a contamination measure developed for this trial will be completed at 3 months. The contamination measure will be completed by participants in both conditions and contains questions on sharing or receiving information regarding the CHANGE intervention, including specific strategies.

Competency of the facilitators was measured through the Enhancing Assessment of Common Therapeutic factors (ENACT) tool [16, 51] as part of the Ensuring Quality in Psychological Support (EQUIP) platform during their training. During the RCT, we will collect process data to investigate fidelity, dose, recruitment rates, retention/completion of follow-up and the feasibility of RCT procedures (e.g. randomisation). Furthermore, fidelity, feasibility, acceptability, and potential sustainability will be further explored in a nested qualitative study using individual semi-structured interviews with supervisors (*N* = 4), facilitators (*N* = 17), participants (*N* = 40), family members (*N* = 20) and outcome assessors (*N* = 11). The interviews will include questions on the experience of engaging with the CHANGE intervention; barriers and facilitators to attendance, delivery of the intervention; acceptability and feasibility, perceived effectiveness of the programme, helpfulness of the intervention; and opportunity costs.

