### Sample size {14}

A sample size of 500 enrolled participants (250 in each arm with 1:1 allocation) will provide 90% power to detect a difference in the PDA from alcohol of 55% in the EUC arm vs 68% in the CHANGE arm (SD = 37%) at 3 months follow-up with alpha = 0.05. The sample size calculation accounts for 20% loss to follow-up at 3 months. The estimated PDA and SD are conservative, based on the CAP trial (54% vs 69%) (Nadkarni et al., 2017).

For the semi-structured interviews, all facilitators (*N* = 17), supervisors (*N* = 4), and outcome assessors (*N* = 11) will be invited to participate, plus 20 family members of intervention completers, 20 intervention completers, 20 participants in the control group, and as many participants who dropped out as possible until saturation is reached. A purposive sampling procedure will be used when selecting these participants to ensure maximum variation.

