## Assignment of interventions: masking

### Who will be masked? {17a}

Throughout the trial, the overall PI (DF) and site PIs (WT and EK), outcome assessors and trial statisticians will be masked to treatment allocation. Participants, intervention facilitators, Village Health Team members and the project coordinator will be unmasked. The local data entry lead will also be unmasked in order to carry out routine data monitoring and cleaning.

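### Masked outcome assessors may be interviewed about CHANGE after the 3-month follow-up while 12-month assessments are still to come, and no safeguard specific to those interviews is given

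*Protocol article*

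**What the plan says.** Five statements in the protocol article bear on this.

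- **Masking.** Who will be masked? {17a} says that, for the duration of the trial, "outcome assessors and trial statisticians will be masked to treatment allocation". Participants are unmasked.
- **Data collection.** Plans for assessment and collection of outcomes {18a} assigns the baseline, 3-month and 12-month data to independent outcome assessors.
- **Interviews.** Participant timeline {13}, in the text after Fig. 3, sets the timing and names the interviewees: "After the 3-month follow-up, qualitative interviews will be conducted with intervention facilitators, outcome assessors, trial participants and family members". The purpose is "to gain knowledge on implementation processes". It adds: "The interviewers will be unmasked and will not be involved in outcome assessments".
- **Who is invited.** Sample size {14}: "all facilitators (*N* = 17), supervisors (*N* = 4), and outcome assessors (*N* = 11) will be invited to participate".
- **Topics.** Outcomes {12}, in the text after Fig. 2, gives one list of interview topics for supervisors, facilitators, participants, family members and outcome assessors together. It covers experience of CHANGE, what helped or hindered attendance, acceptability and feasibility, and ends with "perceived effectiveness of the programme, helpfulness of the intervention; and opportunity costs".

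Procedure for unmasking if needed {17b} refers to operating procedures against unmasking, without giving their content. It also has a rule for replacing an assessor when masking fails for one participant during an assessment.

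**The concern.** A masked assessor has no direct basis for saying whether CHANGE works, whether it helps, or why men did or did not attend. Putting such questions to him invites him to work out which of the men he has met received it, and to settle on a view of whether it worked. If he later carries out 12-month assessments, he brings that guess and that expectation with him.

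The 12-month outcomes are open to this. Percentage of days abstinent at 12 months is a stated secondary hypothesis. AUDIT, K10, PHQ-9, HSCL-A, PCL-6, WHODAS 2.0 and perpetration of intimate partner violence are secondary outcomes at the same visit. All are reports by unmasked participants, collected by an assessor. Assessor masking is therefore the main safeguard against probing or recording that differs by arm.

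The precaution in Participant timeline {13} runs one way. It keeps the unmasked interviewers out of outcome assessment, but says nothing about protecting the masked assessors when they are the ones being interviewed.

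**Working it through.** The point depends on no figure in the plan, so the check sets the sections side by side.

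**1. Can the interviews come before the 12-month assessments?** The only time anchor in Participant timeline {13} is the 3-month follow-up, and no latest date is given. Trial status gives first recruitment on 4 August 2023 and last on 20 November 2023. Assume randomisation close to those dates and ignore visit windows:

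| Visit | First | Last |
|---|---|---|
| 3 months | about 4 November 2023 | about 20 February 2024 |
| 12 months | about 4 August 2024 | about 20 November 2024 |

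From the last 3-month visit to the first 12-month visit is about 20 February to 4 August 2024, or roughly five and a half months. Interviews tied to the 3-month follow-up would naturally fall in that interval. The text permits this order but does not state it.

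**2. Would the interviewed assessors do the 12-month visits?** Sample size {14} invites all 11. Only one assessor group is described, and no separate 12-month team is mentioned. That the same people return is likely but not stated.

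**3. Do the topics reach CHANGE itself?** The list in Outcomes {12} is not divided by interviewee group, so nothing in the article removes effectiveness, helpfulness or attendance from the assessor interviews.

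**4. Do the stated safeguards cover it?** The replacement rule in Procedure for unmasking if needed {17b} is triggered when masking fails for one participant during an assessment. An expectation formed in an earlier interview would not trigger it. If all 11 had been interviewed, a replacement from the same group would be equally exposed. The general operating procedures may help, but their content is not given. The cover is partial.

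**5. How far could it reach?** If 11 of 11 assessors are interviewed before month 12 and the same 11 do all the visits, the share of 12-month assessments done by an interviewed assessor is 11/11 = 100%, that is, up to 500 men before losses. The article gives no 12-month loss. If the 20% assumed at 3 months also held at 12 months, the number would be 500 × 0.80 = 400. If only some accept and caseloads are equal, the share falls in proportion: 6 of 11, for example, gives 6/11 = 55%. These figures count assessments by someone who was interviewed, not by someone who was unmasked.

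**6. Primary outcome.** It is measured at the 3-month follow-up, which the interviews follow, so it is not affected.

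**The case against.** The strongest reply is that the article is not where this detail belongs. Trial design {8} refers the reader to a separate publication for the process evaluation methods. Topic guides by interviewee group, exact timing and the handling of masked interviewees may be set out there. The pooled topic list also contains items that plainly fit participants rather than assessors, such as opportunity costs. The stated purpose is implementation, and Outcomes {12} names recruitment, retention and the feasibility of trial procedures as process subjects, which are the ones assessors can speak to. Restricting assessors to those subjects may already be the practice. Implementation {16c} adds that all staff are trained on the importance of masking.

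Much of this stands, and it limits what can be claimed. A reader might infer several stronger things that the documents do not support:

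- **That interviewers will reveal allocations.** The interviews collect information from assessors. An unmasked interviewer does not by that fact disclose anyone's arm.
- **That assessors will be asked which men attended.** The listed topic is general barriers and facilitators to attendance.
- **That the interviews are fixed before month 12, or that the same 11 people return.** Both are natural readings, but neither is stated.
- **That the masking and interview sections contradict each other.** They do not; an assessor can be interviewed and stay masked.

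What the reply does not remove is what the article itself fixes: masked assessors as interviewees, unmasked interviewers, a 3-month anchor with no upper limit, and a shared topic list that includes perceived effectiveness. A pointer to another publication does not change those statements.

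**Conclusion.** The concern holds as an avoidable risk to assessor masking at 12 months. It rests on two assumptions: that at least some assessor interviews are held before the 12-month assessments, and that interviewed assessors carry out some of those assessments. It would fall away if the assessor topic guide already leaves out the questions about CHANGE.

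The upper limit is all 12-month assessments. The actual extent cannot be worked out from the article, and no direction or amount of bias can be assigned. It would be too strong to conclude that the 12-month outcomes are unmasked, or that assessor masking is the only protection left, given the procedures in {17b} and the staff training in {16c}. Only secondary outcomes are touched. This is an inexpensive improvement to the design, not a flaw that threatens the main conclusion of the trial.

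**What to change.** In Participant timeline {13}, state that outcome assessors will be interviewed after the last 12-month assessment. Alternatively, allow earlier assessor interviews but limit them to trial procedures (recruitment, consent, assessment tools, retention), and state in Outcomes {12} that the topics on CHANGE attendance, effectiveness and helpfulness are not put to assessors. The interviews with facilitators, supervisors, participants and family members can stay as planned.

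The cost is the rescheduling of at most 11 interviews. The downside of deferral is that assessors' recall of the early phase will be older, which the procedures-only interview avoids.

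If the assessor interviews have already been held, report when they took place relative to the 12-month assessments, so that readers can judge the exposure.

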### Sample size {14}

A sample size of 500 enrolled participants (250 in each arm with 1:1 allocation) will provide 90% power to detect a difference in the PDA from alcohol of 55% in the EUC arm vs 68% in the CHANGE arm (SD = 37%) at 3 months follow-up with alpha = 0.05. The sample size calculation accounts for 20% loss to follow-up at 3 months. The estimated PDA and SD are conservative, based on the CAP trial (54% vs 69%) (Nadkarni et al., 2017).

For the semi-structured interviews, all facilitators (*N* = 17), supervisors (*N* = 4), and outcome assessors (*N* = 11) will be invited to participate, plus 20 family members of intervention completers, 20 intervention completers, 20 participants in the control group, and as many participants who dropped out as possible until saturation is reached. A purposive sampling procedure will be used when selecting these participants to ensure maximum variation.

### Recruitment {15}

Rhino and Imvepi refugee settlements contain 85 villages. For our study, household recruitment will be conducted in up to 64 of the villages (excluding villages that are populated by a majority of Muslim refugees (less likely to drink alcohol due to religious reasons), refugees belonging to the Dinka ethnicity (the majority of men have returned to South Sudan), Congolese refugees (speaking different languages), or villages where the implementing partner (HealthRight) has previously recruited male participants for psychological interventions will be excluded). The order of villages to be visited will be randomised a-priori using statistical software. Residents in the villages will be screened until the required sample is reached. The date of first recruitment was the 4th of August, 2023.

## Assignment of interventions: allocations

### Sequence generation{16a}

The randomisation sequence will be generated by a statistician independent of the trial team using Stata 16.0 statistical software (College Station, TX, USA). Randomisation will be stratified by village and will be blocked in random order. Within the villages, participants will be individually randomised 1:1 to both arms of the trial after baseline assessment by the Village Health Teams.

### Concealment mechanism {16b}

Allocation concealment will be maximised using sequentially numbered opaque sealed envelopes, which will hold the randomisation code inside (generated by an independent statistician using statistical software). The envelope seal will be signed over to prevent tampering and will be opened by the Village Health Teams with the participant. Envelopes with evidence of tampering will not be used. All outcome assessors and members of Village Health Teams will be trained on the importance of maintaining the randomisation sequence and spotting tampering. Data monitoring checks will be used to identify irregularities in the sequence in which envelopes are opened.

### Implementation {16c}

Randomisation envelopes will be prepared by the unmasked data lead; each envelope will contain a randomisation code inside and an envelope ID on the outside. The envelope ID will be manually linked to the participant ID in ODK by the outcome assessor following baseline assessment. The outcome assessors will be masked to the randomisation code inside the envelope and will not know the allocation status of the participant. Once the randomisation envelope has been assigned to a participant ID, the outcome assessors will take the participant to the member of the Village Health Team and leave. The Village Health Team member will open the envelope with the participant and explain the next steps, depending on whether they are randomised into the CHANGE intervention and EUC arm, or EUC alone. The Village Health Team will deliver EUC to all participants. All study staff will be trained on the importance of maintaining the randomisation sequence, and masking, and data monitoring checks will be used to identify irregularities in the sequence in which envelopes are opened.

## Assignment of interventions: masking

### Who will be masked? {17a}

Throughout the trial, the overall PI (DF) and site PIs (WT and EK), outcome assessors and trial statisticians will be masked to treatment allocation. Participants, intervention facilitators, Village Health Team members and the project coordinator will be unmasked. The local data entry lead will also be unmasked in order to carry out routine data monitoring and cleaning.

### Procedure for unmasking if needed {17b}

There are strict standard operating procedures in place to avoid unmasking. If masking is compromised for a particular participant during outcome assessment, the assessment will stop and a new independent outcome assessor will conduct the rest of the assessment with the participant. The primary outcome will be measured early on in the survey interview to ensure it is the least likely to be compromised in the case of accidental unmasking.

## Data collection and management

### Plans for assessment and collection of outcomes {18a}

Primary and secondary outcome data, and user cost data will be collected electronically by independent outcome assessors using ODK, on tablets at baseline, 3- and 12-month follow-ups.

At baseline, additional sociodemographic data will be collected. Tablets will be password-protected, and each outcome assessor will have a specific tablet assigned to them. Data that is uploaded will be encrypted. If enrolled, participants are assigned a unique study ID that will be used to identify all participant data during data collection at the three time points.

Data checks will be conducted daily (number of records uploaded), and weekly data reports (variable summaries, summary of missing data) will be created by the data lead.

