OxCAP-MH [37]	Sixteen-item index on wellbeing, covering various domains of individual well-being including overall health, enjoying social and recreational activities, friendship, and support, having suitable accommodation etc. Scored on a scale of 1 to 5	Mean score	Has been contextually validated by the current research team in Rhino settlement (publication forthcoming)
User Cost Questionnaire	Fifteen item measure on household expenditure specifically designed for this trial to measure the opportunity cost of participating in the CHANGE intervention	The opportunity cost of participating in the CHANGE intervention	Specifically designed and piloted for this trial. Based on the iMTA productivity loss of cost questionnaire [50]

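### Two instruments that ask about CHANGE can unmask the outcome assessors at 3 months, and nothing keeps an unmasked assessor from seeing the same man at 12 months

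*Protocol article*

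**What the plan says.** Who will be masked? {17a} states that "outcome assessors and trial statisticians will be masked to treatment allocation", and the sentence applies to the whole trial. Participants, facilitators and Village Health Team members are unmasked.

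Plans for assessment and collection of outcomes {18a} states: "Primary and secondary outcome data, and user cost data will be collected electronically by independent outcome assessors using ODK". The same sentence gives the timing and means as "on tablets at baseline, 3- and 12-month follow-ups". Table 2 describes the user cost questionnaire as fifteen items on household expenditure, "specifically designed for this trial to measure the opportunity cost of participating in the CHANGE intervention", and gives that same cost as its outcome. Table 1 lists it among the health economic indicators, under secondary outcomes, at 3 and 12 months.

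Outcomes {12} adds, in the text after Fig. 2, that "a contamination measure developed for this trial will be completed at 3 months". This measure is "completed by participants in both conditions and contains questions on sharing or receiving information regarding the CHANGE intervention, including specific strategies". No administrator is named, but the section opens by saying that outcome assessors collect the data at baseline, 3 and 12 months.

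Procedure for unmasking if needed {17b} refers to standard operating procedures and gives two safeguards. First, "If masking is compromised for a particular participant during outcome assessment, the assessment will stop" and another independent assessor finishes it. Second, the primary outcome is asked early in the interview.

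**The concern.** The masked staff are asked to collect answers about taking part in the treatment to which they are masked. {17b} is framed around accidental unmasking, whereas this exposure is part of the planned battery.

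Assessor masking matters here because the outcome measures are self-reports collected in an interview and the participants know their arm. A masked interviewer is the main protection against prompting, probing or recording that differs between arms. If an assessor learns a man's arm at 3 months and interviews him again at 12 months, that protection is gone for his 12-month PDA, AUDIT, K10, PHQ-9 and the other scales. The single-blind description would then hold less well for the 12-month results than for the 3-month primary outcome.

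**Working it through.** The protocol gives no figure for masking, so the check sets the sections side by side.

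**1. Can the user cost questionnaire unmask?** {17a} masks assessors throughout, {18a} has them collect user cost data at both follow-ups, and Table 2 says that the tool measures the cost of taking part in CHANGE. Intervention description {11a} gives six weekly sessions of about 90 minutes, so 6 × 90 = 540 minutes of session time in the CHANGE arm and none under enhanced usual care alone. A tool that captures this cost will draw different answers from the two arms. Its use at baseline, before randomisation, reveals nothing. The 3- and 12-month uses can.

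**2. Can the contamination measure unmask?** It goes to both arms, so being asked the questions reveals nothing. The answers may: a man who attended sessions can describe strategies first-hand. Whether an outcome assessor hears those answers is an inference from the opening of Outcomes {12}.

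**3. What do the {17b} safeguards cover?**

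| Outcome | Protection in {17b} |
|---|---|
| 3-month PDA (primary) | Asked early, so largely protected |
| Later scales in the same 3-month interview | Assessor replaced if unmasking is recognised |
| 12-month PDA and other 12-month outcomes | The same two rules within that interview; nothing about an assessor who already learned the arm at 3 months |

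The gap is in the last row. The replacement rule ends with the interview in which the unmasking occurred. The protocol neither says that the same assessor returns at 12 months nor prevents it.

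**4. How many men could be affected?** Inputs from Sample size {14} are 250 men per arm and 20% loss at 3 months, and the number of assessors is 11.

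- CHANGE men interviewed at 3 months: 250 × (1 − 0.20) = 200. This is a ceiling. It requires every one of them to reveal his arm and to meet the same assessor again.
- If 12-month visits were assigned at random among the 11 assessors (an assumption): 200 / 11 ≈ 18 men would meet the same assessor.

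The number of repeat pairings in the CHANGE arm therefore runs from about 18 to 200 across these two assignment rules. It would be lower with further loss by 12 months, for which {14} gives no figure, and zero under a rotation rule. These are counts of opportunities for bias and say nothing about its size.

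**5. Does the protocol already use this kind of separation?** Yes. Under Implementation {16c} the assessor leaves before the envelope is opened. Under Participant timeline {13} the qualitative interviewers are unmasked and kept out of outcome assessment. The two instruments at issue have no stated equivalent.

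**The case against.** The best case for the protocol has four parts.

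- **The items are not shown.** The user cost tool is described as covering household expenditure, is based on a productivity-loss questionnaire and is also used before randomisation, so it cannot consist only of questions about attending CHANGE. A control participant who heard about CHANGE from a neighbour could also answer yes on the contamination measure. This stands: a reader might infer that the answers always give away the arm, or that {17b} would halt most CHANGE-arm interviews, but the text supports only that they can reveal allocation.
- **The contamination measure has no named administrator**, and {18a} does not list it among the data that assessors collect. This stands, so the user cost questionnaire carries the main weight.
- **{17b} does protect more than the primary outcome.** A reader might infer that scales asked later in the same interview are unprotected, but the replacement rule covers them once unmasking is noticed. Module order may also be set in the operating procedures, which are not shown. This narrows the point to the link between 3 and 12 months.
- **A repeat pairing is not stated**, and an assessor would have to remember one man's arm for nine months. This is fair, and it limits the likely number affected. With 11 assessors, though, repeat pairings are plausible unless they are ruled out.

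A reader might also attach a bias to this, for example by assuming a shift of 0.05 to 0.20 SD and multiplying by the SD of 37: 1.9 to 7.4 PDA points, or 14% to 57% of the 13-point target difference. The protocol does not support that. The shift is invented, the SD and the 13 points are 3-month planning values, and the sum treats every CHANGE man as unmasked and seen again by the same assessor.

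**Conclusion.** The point holds as a gap in masking at 12 months. Staff described as masked throughout collect at least one instrument built around taking part in CHANGE, and the unmasking procedure does not carry over from the 3-month to the 12-month visit. The 12-month secondary outcomes, including PDA, are exposed. The 3-month primary outcome is largely protected, and nothing here undermines it.

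The conclusion rests on two assumptions: that the user cost items elicit what Table 2 says they measure, and that assessors may see the same man twice. The size of any bias cannot be derived from the documents. The change is a cheap improvement and does not correct an error in the primary analysis.

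**What to change.** 1. Place the user cost and contamination modules in a separate ODK form that opens only after all other outcome measures have been submitted, at 3 months and, for user cost, again at 12 months. Say in the protocol who administers the contamination measure.
2. At 12 months, assign each participant to a different one of the existing 11 assessors than the one who saw him at 3 months. If an assessor was replaced during the 3-month interview, exclude both.
3. Record the assessor's guess of allocation at the end of each interview and report it by arm. A guess taken after the two modules shows what the assessor knew on leaving, and so may overstate what was known while the outcomes were recorded. The report should say so.

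If the 3-month interviews are already complete, steps 2 and 3 and the 12-month part of step 1 can still be applied. The cost is splitting the form, a scheduling constraint at 12 months and one added item per interview. No extra staff are needed, and sample size, outcomes and treatment do not change. Handing the modules to unmasked staff is not recommended: the qualitative interviewers are barred from outcome assessment under {13}, and leaving both follow-up waves to the project coordinator would not be cheap.
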